### Objectives

Aims and hypotheses to be tested:
On the group level, is social skill intervention using music therapy more effective in enhancing social interaction than non-musical social skill training for children with ASD and co-occurring mild/borderline ID?On the individual level, are participants with enhanced left-lateralized FAA to social scenes relative to baseline more responsive to both types of social skill interventions?For participants in the music therapy intervention, does enhanced left-lateralized FAA to preferred music relative to baseline predict better outcomes in social skill development?

## Methods/design

### Study design

The proposed study will be a randomized controlled trial with two parallel groups. Recruited children will first be screened for eligibility and then matched into pairs by age and gender by a research assistant. Another research assistant will assign individuals in each pair to the treatment group (social skill intervention with music) or control group (non-musical social skill intervention) using random number sequences. Participants in the same condition will then be separated into groups of eight by drawing lots. The research assistants performing participant matching and randomization will not be involved in data collection or outcome assessments. The pre-tests and post-tests will include (i) childhood autism rating scale-second edition (CARS-2) rated by an independent rater, (ii) social responsiveness scale-second edition (SRS-2) rated by parents, and (iii) EEG recording. Pre-tests will be administered 2 weeks before intervention, while post-tests will be administered 2 weeks and 4 months after intervention. In each intervention week for 12 weeks, the participants will undergo one 45 min session of social skill training. Within each condition, the same trainer will be responsible for all sessions to minimize differences in intervention delivery across groups. The intervention sessions will be videotaped, and social behavior in the first and last sessions will be coded offline. Figure 1 shows an overview of the study design. Should protocol modifications become necessary, the amendments will be communicated to relevant parties, including research personnel, intervention trainers, participants and their parents, the trial registry, the journal that published the study protocol, and the funding body.

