### Outcome measures

#### Primary outcomes

The primary outcome measure is autistic severity as assessed using a standardized rating scale by an independent rater who will be blinded to the study group allocation. This outcome was selected because observing behavioral changes that generalize to other social contexts outside of the intervention is the ultimate goal of social skill intervention. Parental rating by using a standardized rating scale is included as another outcome to support the clinical assessment. Parents are good informants because they spend time with the participants outside of intervention contexts, but they are not blinded to the group assignment and may exhibit expectation biases. Another outcome is the behavioral changes at the last intervention sessions relative to the first session. Trained research assistants who are blinded to the session number and study hypotheses will code for target social behaviors by using video data. This measurement will provide an objective measure of the social skills exhibited by participants within the intervention setting.

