##### SRS-2

Parental ratings of generalized social interaction outcomes will be collected using SRS-2. A parent of each participant will be asked to complete the SRS-2 based on their observations of their child over the previous 3 months. The scale is a 65-item questionnaire that measures the severity of social impairments associated with ASD [17]. The five subscales include social awareness, social cognition, social motivation, social communication, and autistic mannerisms. Each item is rated on a scale from “0” (never true) to “3” (almost always true), and high scores indicate severe social impairments. SRS-2 exhibits good psychometric properties in Western and Chinese contexts and is sensitive to changes in social functioning among children with ASD [17, 18].

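### The described order implies allocation before the pre-test, and nothing keeps it from unblinded parents until they have completed the baseline SRS-2

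*Protocol article*

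**What the plan says.** The Study design section of the protocol article sets out the steps in this order:

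1. Screening and matching: "Recruited children will first be screened for eligibility and then matched into pairs by age and gender by a research assistant".
2. Randomisation: "Another research assistant will assign individuals in each pair to the treatment group" or to the control group.
3. Formation of intervention groups: "Participants in the same condition will then be separated into groups of eight by drawing lots".
4. Assessments, among them the "social responsiveness scale-second edition (SRS-2) rated by parents", with this timing: "Pre-tests will be administered 2 weeks before intervention, while post-tests will be administered 2 weeks and 4 months after intervention".

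On blinding, the Primary outcomes section gives the CARS-2 rating to "an independent rater who will be blinded to the study group allocation". The Secondary outcomes section says that the EEG data collectors are also unaware of the group. Of parents, the Primary outcomes section says that "they are not blinded to the group assignment and may exhibit expectation biases", and it does not limit this to the post-tests.

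The SRS-2 section describes the instrument as a recall rating: "A parent of each participant will be asked to complete the SRS-2 based on their observations of their child over the previous 3 months". The Abstract names SRS-2 as a primary outcome together with CARS, and says that the mixed models use the pre-intervention session and both post-intervention sessions. The Statistical analyses section lists intervention type and time (pre and post) among the fixed effects.

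**The concern.** Once treatment starts, parents cannot be blinded to music or non-music training, and the article concedes the resulting expectation bias. The baseline is different. It is the one parent rating that could be kept free of allocation knowledge, simply by collecting it early enough. If the steps are carried out in the order in which they are described, that protection is lost.

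The SRS-2 is a subjective rating of the past three months, and some families are to be recruited through music therapy centers, so a preference for one arm is plausible. Parents who know that their child will have music therapy might describe the starting point differently from parents who know that their child will not. Because the pre-test is one of the time points in the model, such a difference would enter the SRS-2 treatment effect. It would come on top of the post-treatment expectation bias that the article already admits.

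**Working it through.** **Is the order fixed by the text?** The order words (first, then, then) link screening, matching and the drawing of lots, with random assignment described between matching and lots. The pre-tests come next in the description but carry no order word that ties them to randomisation. Their only anchor is two weeks before intervention. No section places the pre-test before randomisation, and the Participants section ties consent only to enrolment into the interventions. Randomisation first is therefore the natural reading, but it remains an inference.

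**Who is protected at baseline?**

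| Measure | Rater or collector | Stated blinding |
|---|---|---|
| CARS-2 | Independent rater | Blinded |
| EEG | Research assistants | Blinded |
| SRS-2 | Parent | Not blinded, no time limit given |

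Only SRS-2 is exposed.

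**What would a distorted baseline do?** The article states no figure for this, so there is none to reproduce. Let b be the between-arm shift in baseline SRS-2 (in SD units) caused by knowing the allocation and not carried over to the post-test. Let r be the pre-post correlation, with equal SDs at both times. The documents give neither b nor r; I assume b = 0.1 to 0.3 and r = 0.5 to 0.8. The article does not spell out the SRS-2 contrast, so I take the two usual ones.

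- Change from baseline: bias = b in absolute size.
- Baseline-adjusted: bias ≈ r × b.

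For scale, the Sample size calculation section plans on an effect of 0.71: 0.1/0.71 = 14.1%, 0.2/0.71 = 28.2%, 0.3/0.71 = 42.3%.

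To see the effect on error rates, take 40 × (1 − 0.25) = 30 completers per arm. The standard error of the change contrast is √(2 × 2(1 − r)/30), which is 0.258 for r = 0.5, 0.200 for r = 0.7 and 0.163 for r = 0.8. With no true effect, the rejection rate of a nominal two-sided 5% test is 1 − Φ(1.96 − b/SE) + Φ(−1.96 − b/SE).

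| b (assumed) | Bias, change contrast | Bias, baseline-adjusted (r = 0.5 / 0.7 / 0.8) | Actual error of change contrast (r = 0.5 / 0.7 / 0.8) |
|---|---|---|---|
| 0.1 | 0.1 | 0.05 / 0.07 / 0.08 | 6.7% / 7.9% / 9.4% |
| 0.2 | 0.2 | 0.10 / 0.14 / 0.16 | 12.1% / 17.0% / 23.2% |
| 0.3 | 0.3 | 0.15 / 0.21 / 0.24 | 21.3% / 32.3% / 45.1% |

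This treats children as independent and ignores the pairing and the groups of eight. It shows the mechanism and is not a forecast.

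**The case against.** The strongest objection is that the sequence is inferred. The Study design section may be arranged by topic (allocation, assessments, sessions, video) and not strictly by time. No sentence says that the pre-test follows randomisation, or when parents learn the allocation. Figure 1, which gives the design and enrolment overview, is not shown and may settle the matter. The sentence quoted for screening and matching mentions neither randomisation nor the pre-test; the two steps after it carry the sequence. All of this stands, and it is why the point is put as what the text implies.

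It can also be said that a condensed article may leave the timing of disclosure to the full protocol. That has some force. But this article does set out a sequence and separately admits parental bias, and read together the two leave the baseline exposed. The CARS-2 rater and the EEG collectors receive explicit protection; the parent baseline does not.

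On impact, three counter-arguments hold. The shift of 0.1 to 0.3 SD is purely assumed, and similar shifts in both arms would cancel, which is possible because both arms receive free active training on the same schedule. The 0.71 is a meta-analytic effect for generalised social interaction and not an SRS-2 effect, so the percentages only give a scale. And the Primary outcomes section treats the blinded CARS-2 rating as the leading measure, with SRS-2 in support.

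A reader might infer that the damage could never be undone in analysis. That goes too far: a comparison of post-test SRS-2 alone between the randomised arms does not use the baseline, so a distorted baseline cannot bias it. It would lose the precision gained from the baseline, and the conceded post-treatment expectation bias would remain.

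**Conclusion.** The point holds in a limited form. The described order implies allocation before the pre-test, parents are stated to be unblinded, and nothing in the text keeps the allocation from them until they have completed the baseline SRS-2. A resulting baseline shift would enter the pre/post treatment contrast in full for a change analysis, and by about r × b with baseline adjustment. Its size and direction are unknown; the figures above rest on assumed b and r and on 30 completers per arm.

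Two stronger readings are tempting. One is that the protocol states as fact that children are randomised and grouped before the pre-test and that parents then know the arm; the text only suggests this. The other is that the baselines of the trial generally are compromised; the stated blinding of the CARS-2 rater and the EEG collectors rules that out. What remains is an avoidable exposure in a listed primary outcome, worth correcting because the remedy is specific and cheap.

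**What to change.** State in the Study design section that the parent SRS-2 pre-test is completed before the pair is randomised. If scheduling needs earlier randomisation, state that the allocation is not disclosed to families until that rating is in; for a pair, the simplest rule is to wait for both children. Make the text and Figure 1 agree. If the figure already shows the pre-test before allocation, only the text needs to change.

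The cost is that allocation notices go out slightly later, within the two weeks before session 1. Randomising only after the pre-test would also put matching, assignment and the drawing of lots into that window. If this is too tight, withholding disclosure gives the same protection of the parent rating without moving those steps.

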### Sample size calculation

The sample size was calculated based on the predicted effect size of 0.71 in generalized social interaction outside intervention context from a meta-analysis of social skill intervention studies using music therapy for children with ASD (aged 2–12) relative to non-music intervention or standard care controls [7]. For a two-group *t* statistics with α = 0.05, power = 0.8, and attrition rate = 25%, a minimum number of 33 participants in each group will likely yield statistically meaningful differences. Given that neural measures can detect autonomic responses and behavioral intentions in addition to explicit actions, they can be considered more change sensitive than behavioral observations. Hence, we expect that recruiting 40 participants in each group will allow us to detect presence of effects in qEEG measures.

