### Statistical analyses

Interim analyses will not be performed and data collection will continue until the intended sample size is reached. The investigators and research assistants will have full access to the final trial dataset. Analyses will focus on hypothesis-driven testing with separate models for each outcome measure by using linear mixed effect modeling if the assumptions for linear effects are met [21]. This regression-based statistical test can be used to evaluate multiple categorical and continuous predictors, and eliminates the need to run multiple tests for different hypotheses, which inflates the risk for type I error. Attrition bias will be assessed by comparing the participant completion rate in the two conditions and considering the reasons. Mixed effect models are robust with missing or extreme values, which is useful if the attrition rate for the 12-week intervention is higher than expected. Fixed effect predictors will be intervention type (music/non-music), time (pre−/post-intervention), and pre-treatment EEG frontal asymmetry (social and music). The random effects of participants and groups will be included to estimate random errors arising from individual differences in participants and group trainers. Control factors will include overall and verbal IQ, age, and ASD severity. The inclusion of these covariates alleviates concerns on unreliable effects due to the heterogeneity of children with ASD and ID.

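### Children are randomised within pairs matched on age and gender, but the stated model carries only age; the reported standard error may be slightly too large, with no threat to validity

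*Protocol article*

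**What the plan says.** Under Study design, the protocol article has recruited children "matched into pairs by age and gender by a research assistant". Allocation then happens inside the pair: "Another research assistant will assign individuals in each pair to the treatment group (social skill intervention with music) or control group". Therapy groups are formed afterwards, within arm: "Participants in the same condition will then be separated into groups of eight by drawing lots".

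Under Statistical analyses, the fixed predictors are intervention type, time and pre-treatment frontal asymmetry. The random part is described as follows: "The random effects of participants and groups will be included to estimate random errors arising from individual differences in participants and group trainers". The covariates are listed as: "Control factors will include overall and verbal IQ, age, and ASD severity".

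The Sample size calculation uses an unpaired two-group t test with a "predicted effect size of 0.71 in generalized social interaction outside intervention context".

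**The concern.** The pair is the randomisation block, and age and gender define it. A factor that restricts randomisation normally enters the analysis. Otherwise the balance it creates is real but is not credited in the reported standard error, so the interval is too wide and the test conservative. Here one matching factor (age) is in the model. The other (gender) and the block itself (the pair) are not, and no reason is given.

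The random effect for groups cannot stand in for the pair. It refers to the therapy groups and their trainers, and the two members of a pair are in different arms and so always in different therapy groups.

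What is at stake is a modest amount of precision that the trial has already paid for by matching.

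**Working it through.** **The plan's own figure.** With d = 0.71, two-sided α = 0.05 and power 0.8, an unpaired t test needs 32.13, so 33 per group. This equals the stated minimum, but before attrition. At 40 per group, unpaired power is 88.0% with no dropout and 77.2% with 40 × 0.75 = 30 completers. None of these figures takes credit for matching.

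**Side by side.** Randomisation uses pair, age and gender. The model uses age, with overall IQ, verbal IQ and ASD severity. Missing from the model: gender and pair.

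**Inputs that the documents do not give.** The variance explained by age and gender, the sex ratio and the closeness of matching are all assumed: age 5–20%, gender 2–10%, 80% boys, and ages within a pair at most about one year apart. IQ and ASD severity are left out of the calculation.

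**Closed form, single post-treatment outcome, unit variance, n = 40 per arm.** With a and g the variance shares of age and gender:

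- Unadjusted SE = √(2/40) = 0.2236.
- Reported SE with age only ≈ 0.2236 × √(1 − a).
- Reported SE with age and gender ≈ 0.2236 × √(1 − a − g).
- Inflation = √[(1 − a)/(1 − a − g)].

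| a / g | SE, age only | SE, age + gender | Inflation |
|---|---|---|---|
| 5% / 2% | 0.218 | 0.216 | √(0.95/0.93) = 1.011 |
| 10% / 5% | 0.212 | 0.206 | √(0.90/0.85) = 1.029 |
| 20% / 10% | 0.200 | 0.187 | √(0.80/0.70) = 1.069 |

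**Simulation of 40 matched pairs, 3,000 runs per scenario, d = 0.71 for power.** Mean reported SEs agree with the closed form: 0.217 vs 0.215, 0.211 vs 0.205 and 0.199 vs 0.186.

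| a / g | Power, no dropout (age only vs age + gender) | Power, 25% dropout | Type I error, no dropout |
|---|---|---|---|
| 5% / 2% | 91.0% vs 91.4% | 78.8% vs 79.5% | 4.8% vs 5.2% |
| 10% / 5% | 90.8% vs 91.7% | 81.0% vs 82.5% | 4.4% vs 4.9% |
| 20% / 10% | 95.7% vs 96.6% | 86.3% vs 90.0% | 3.8% vs 5.1% |

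The simulation error on a 5% rate is √(0.05 × 0.95/3000) ≈ 0.4 points, so conservatism is clear only in the last row. In that row, under no effect and without dropout, the actual spread of the estimate is 0.187 under either model. The estimate keeps the benefit of matching, and only the reported SE differs.

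**Any pair correlation ρ that the covariates leave unmodelled.** Inflation is 1/√(1 − ρ): 1.010, 1.026, 1.054 and 1.118 for ρ = 0.02, 0.05, 0.10 and 0.20.

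**Arm-by-time contrast.** A stable gender or pair effect on level cancels from post minus pre, and the participant effect already absorbs it. A small simulation had 30 runs, 3 visits, pair variance 0.15, gender effect 0.7, participant variance 0.4, residual variance 0.35 and no therapy-group term. The SE was 0.188 both without and with pair and gender, and with 25% dropout it was 0.207 without and 0.206 with.

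**The case against.** The strongest objection is that the planned model is longitudinal. The pre-test is one of the modelled time points, and participants have a random effect. If the treatment effect is the arm difference in change, a pair intercept and a gender main effect add almost nothing, as the last check shows. This stands for that contrast. It does not settle the matter, because the Statistical analyses section lists intervention and time without their interaction. For an intervention main effect, or for a baseline-adjusted post-treatment comparison, the gain is real.

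It is also fair to say that age, IQ and ASD severity are already in the model, that the error is on the conservative side, and that the sample size takes no credit for matching, so no promised power is lost. All of this limits the size of the point.

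The article is condensed, and its list of control factors need not be exhaustive. But it names its random effects and covariates, including one matching factor and not the other, and nothing in it points to a pair or gender term.

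A pair term can be awkward: pairs hold two children at most, they cross with therapy groups, and the variance may be estimated at zero. That is a reason for a fallback, not for leaving gender out.

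**Conclusion.** The stated model does not fully reflect the randomisation. It carries age but not gender or the pair. Under the assumed variance shares and a single post-treatment outcome, the reported SE is about 1–7% too large. The power loss is about 0.4–1 point without dropout and 0.7–3.7 points with 25% dropout. For an arm-by-time contrast the loss is near zero unless gender or pair affects change. The change is worth making because it is nearly free, not because the loss is large.

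A reader might infer more, and the documents do not support it:

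- That the analysis ignores the randomisation altogether. It does not, since age is a covariate and the balance stays in the estimate.
- That the SE is 5%, 12% or 20% too large. Those values are 1/√(1 − r) for r = 0.1, 0.2 and 0.3. They compare a paired with an unadjusted analysis of one outcome, and r would have to be the correlation left after the planned covariates, which the documents do not give.
- That this explains power below 80%. The 77.2% comes from 25% attrition at 40 per group, which is a separate sample-size matter.

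**What to change.** Add gender to the control factors in every between-arm model. Include the matched pair as a random effect, crossed with therapy group. Fit the model to all available children, so that a child whose partner drops out is kept. If the pair variance is estimated at zero, fall back to age and gender as fixed effects.

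State the contrast that tests the intervention. If it is arm-by-time change, let the added terms act on change, either through gender-by-time and pair-by-time terms or through a post-treatment model adjusted for baseline.

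Do not restrict the analysis to complete pairs. With 25% dropout, that gave power of only 64%, 68% and 77% in the three scenarios, below the planned model in each.

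The cost is a line or two of model specification, a few extra parameters and a possible zero variance estimate. Gender and pair membership must already be known for the matching, so no new data are needed.

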**Fig. 1 Fig1:**
[figure not shown]
Study design and participant enrolment

### Participants

A total of 80 primary school aged children (aged 6–13 years) with ASD and mild/borderline ID will be recruited from various sources, including local special schools, music therapy centers, parent groups, and non-governmental organizations (NGOs) in Hong Kong. A research assistant will obtain written informed consent and oral assent from parents and participants, respectively, before participants enroll into the interventions. Participants and their families’ personal information will be kept strictly confidential and stored securely. Participants and families will receive interventions free of charge and stipends for transportation to the intervention and assessment sites. Participants will also be given souvenirs after pre- and post-intervention assessments as incentives.

